#### Secondary outcomes

The secondary outcomes include the following:The incidence of adverse cardiovascular events (hypotension, severe bradycardia, hypertension, tachycardia, and arrhythmia).The cumulative doses of vasoactive drugs used per patient.Hemodynamic parameters (HR, MAP, SBP, DBP), BIS index, lactic acid, and glucose valuesIncidence and degree of injection pain is measured using a 4-point graded scale: 0 = no pain, 1 = verbal complaint of pain, 2 = withdrawal of the arm, 3 = both verbal complaint and withdrawal of the arm.Incidence and degree of myoclonus is recorded as follows: 0 = no myoclonic movements, 1 = minor myoclonic movements, 2 = moderate myoclonic movements, 3 = major myoclonic movements [16].

### Quality control

The principal investigator, study coordinator, and Office of Scientific Research at the Affiliated Hospital of Guizhou Medical University are jointly responsible for all aspects of the study protocol and amendments. Data collection and follow-up will be performed by two dedicated research residents. Designated trial monitors will periodically review all investigational data for accuracy and completeness to ensure protocol compliance.

### Data collection

Each participant’s characteristics, including age, sex, and body weight, as well as ASA grade, type and duration of surgery, vital signs, cumulative doses of vasoactive drugs, and the incidence of adverse events during induction, will be recorded in a designed data form by an investigator who is blinded to this study.

### Sample size

The sample size calculation was based on the primary outcome, the fluctuations in hemodynamic parameters (▴MAP). Based on our pilot data and relevant literature, assuming a type I error protection of 0.05 and a power of 0.90, 31 patients in each group are required in this study. Considering an estimated 20% dropout rate, 39 patients in each group will be included in this study.

### Statistical analysis

Statistical analysis will be performed by SPSS 22.0 software (SPSS Inc, Chicago, IL, USA). Data distribution will be tested for normality using the Shapiro-Wilk test. Continuous data will be presented as mean [standard deviation (SD)] when normally distributed or median (interquartile range [IQR]) when not normally distributed; Numerical variables will be compared using one-way analysis of variance (ANOVA) or repeated-measures ANOVA or Kruskal-Wallis tests after checking the normal distribution. Post hoc tests will be performed using a Bonferroni method. Categorical variables will be compared using a Fisher’s exact test or chi-square test, as appropriate. A *p* value < 0.05 is considered statistically significant.

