### Interventions

All patients will routinely fast for 8h before surgery. After the patient enters the operating room, standard anesthesia monitoring including electrocardiogram (ECG), noninvasive blood pressure (NIBP), peripheral oxygen saturation (SPO_2_), and bispectral index (BIS) will be routinely monitored. A 20-gauge intravenous cannula will be placed for Ringer lactate (10 ml/kg) infusion. Invasive arterial blood pressure (IBP) will be continuously monitored via insertion of a catheter into the left radial artery under local infiltration anesthesia with lidocaine. After preoxygenation, patients in Group E will be induced with etomidate (0.3 mg/kg), Group LR will be induced with remimazolam (0.2 mg/kg), and Group HR will be induced with remimazolam (0.3 mg/kg). Then, sufentanil (0.5 μg/kg) will be injected in all groups. After that, all patients will be injected with rocuronium (0.6 mg/kg) for muscle relaxation when loss of consciousness. Tracheal intubation will be performed two minutes after rocuronium administration.

Systolic blood pressure (SBP), diastolic blood pressure (DBP), mean arterial pressure (MAP), and heart rate (HR) will be measured and recorded at baseline (T0), 1 min after the induction of anesthesia (T1), 3 min after the induction of anesthesia (T2), immediately at tracheal intubation (T3), 1 min after tracheal intubation (T4), and 5 min after tracheal intubation (T5). Laryngoscopy and anesthesia administration will be performed by an anesthesiologist who is blinded to the study groups. The duration of laryngoscopy and intubation are also recorded for each patient.

Hypotension is considered when MAP falls below 60 mmHg or decreases to less than 20% of baseline during induction, and 50 μg norepinephrine will be given intravenously as needed. When HR decreases below 45 beats per min (bpm), it is considered severe bradycardia and 0.25 mg atropine or more will be administrated by intravenous injection. If the MAP rises above 120 mmHg, nitroglycerin will be given, and once HR rises above 120 bpm, esmolol will be given. The incidence of adverse cardiovascular events (hypotension, severe bradycardia, hypertension, tachycardia, and arrhythmia) and the cumulative doses of vasoactive drugs will be recorded.

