### Outcomes

#### Primary outcome

The primary outcome of this study are the resultant changes in hemodynamic parameters: a) ▴MAP, defined as the difference of maximum or minimum MAP to baseline; b)▴HR, defined as the difference of maximum or minimum HR to baseline.

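### Free improvement: none of the tests listed for numerical variables adjusts the MAP and HR changes for the T0 value already recorded in every patient

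*Protocol article*

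**What the plan says.** The Primary outcome section of the protocol article names two changes. The MAP change is "defined as the difference of maximum or minimum MAP to baseline" and the HR change is "defined as the difference of maximum or minimum HR to baseline".

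The Interventions section states that blood pressure and heart rate "will be measured and recorded at baseline (T0") and at T1 to T5, so the baseline value of each primary variable is available for every patient.

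The Statistical analysis section first says: "Data distribution will be tested for normality using the Shapiro-Wilk test". It then says: "Numerical variables will be compared using one-way analysis of variance (ANOVA) or repeated-measures ANOVA or Kruskal-Wallis tests after checking the normal distribution". Post hoc comparisons use Bonferroni. The article mentions neither ANCOVA nor a baseline covariate. The Sequence generation section describes computer-generated random numbers at 1:1:1 and mentions no stratification by baseline haemodynamics.

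**The concern.** A change score subtracts the whole baseline, which amounts to fixing the regression slope of the follow-up value on baseline at 1. The true slope is usually below 1, so the change stays negatively correlated with its own baseline. Comparing changes without a covariate leaves that correlated part in the residual variance. If one arm happens to start with a higher mean MAP, its mean change is also pulled downwards.

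The article describes no design feature that would balance baseline MAP or HR, so only the analysis can remove such an imbalance. Precision is at stake: confidence intervals are wider and power lower than the same patients can give, and the observed contrast carries a shift due to chance.

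A second, smaller issue is that the test depends on a Shapiro-Wilk result. The primary comparison could then be of means or of ranks, decided by the data.

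**Working it through.** **The plan's own figures.** The Sample size section says: "assuming a type I error protection of 0.05 and a power of 0.90, 31 patients in each group are required in this study". The dropout step reproduces: 31/0.8 = 38.75, rounded up to 39, and 3 × 39 = 117. The 31 itself cannot be reproduced, because the article gives no effect size or SD. The point does not depend on it.

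**Assumed inputs (not in the documents).**
- rho, the correlation between T0 and the extreme value: 0.3 to 0.9.
- Equal SD s at T0 and at the extreme value, and a signed change to a single value.
- 31 per group corresponds to 90% power for a two-sided pairwise t-test at alpha 0.05 (60 degrees of freedom). Solving the noncentral t distribution gives d = 0.837. If a three-group F test was used instead, the implied effect is Cohen's f = 0.375.

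**Variance ratio.** Var(change) = 2s²(1 − rho). Var(ANCOVA residual) = s²(1 − rho²). The ratio is (1 + rho)/2.

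**Power with 31 per group.** Replace d by d/√ratio. The Bonferroni level for three pairwise contrasts is 0.05/3 = 0.0167.

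| rho | Variance ratio | 31 adjusted patients equal, unadjusted (31/ratio) | Power, alpha 0.05 | Power, alpha 0.0167 |
|---|---|---|---|---|
| no adjustment | 1 | 31 | 90% | 79.4% |
| 0.3 | 0.65 | 47.7 | 98.0% | 94.4% |
| 0.5 | 0.75 | 41.3 | 96.3% | 90.6% |
| 0.7 | 0.85 | 36.5 | 94.0% | 86.3% |
| 0.9 | 0.95 | 32.6 | 91.4% | 81.7% |

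The three-group F test at alpha 0.05 gives nearly the same powers: 98.3%, 96.5%, 94.2% and 91.5%. The unadjusted standard error is √(1/ratio) times the adjusted one, that is, 24% larger at rho 0.3 and 3% larger at rho 0.9.

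**Unequal SDs.** If the extreme value has k times the baseline SD, the ratio is k²(1 − rho²)/(k² + 1 − 2·rho·k). For k of 0.7 to 1.3 and rho of 0.3 to 0.7 it runs from 0.42 to 0.99. The gain may be large or almost nil, but it is not negative.

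**Taking an extreme over several readings.** A simulation used the minimum of five readings, an assumed SD of 12 mmHg, 31 per group, and rho of 0.3, 0.5 and 0.7 at each reading. It gave variance ratios of 0.59, 0.71 and 0.82, close to the formula.

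**Chance imbalance.** With equal SDs, each 1 mmHg of baseline difference between two arms shifts the contrast in the MAP change by −(1 − rho) mmHg. With an assumed baseline SD of 10 to 15 mmHg, the baseline difference has standard error SD × √(2/31) = 2.54 to 3.81 mmHg. Its 95% range is ±1.96 times that, about ±5.0 to ±7.5 mmHg. At rho 0.5 the shift can therefore reach about 2.5 to 3.7 mmHg.

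**The case against.** **The plan is valid as it stands.** In a randomised trial, an unadjusted comparison of changes is unbiased on average and keeps its type I error. Chance imbalance is already reflected in the standard error. This stands in full. A reader might infer that the primary result would be biased or the p value wrong, but nothing in the article supports that.

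**Model details usually belong in an analysis plan, and this is a condensed article.** This stands in part. The article assigns no test to the MAP or HR change. One-way ANOVA or Kruskal-Wallis is the natural reading for one value per patient, but it is a reading and not a statement. The point survives because the article does list its tests, and none of them includes the covariate.

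**The gain is unknown.** This stands. Neither rho nor the effect size is given, and at rho 0.9 or with a larger follow-up SD the gain is slight.

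**The outcome is loosely defined.** The article does not say which extreme counts, or whether the change is signed. The formula (1 + rho)/2 needs a signed change to one value. Simulation still showed a gain when the change was taken to the farther extreme or as an absolute value, so the looseness limits the exact figures but not the recommendation.

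**Serial readings.** A reader might infer that the T0 to T5 series would fall back on a Kruskal-Wallis test that ignores within-patient correlation. The article does not say so. Repeated-measures ANOVA is listed, and a Kruskal-Wallis test between arms at one time point uses one value per patient.

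**Conclusion.** The point holds as an improvement available at no cost, not as an error. The listed tests omit a baseline value that the trial already collects and that bears directly on both primary outcomes.

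Under equal SDs and a signed change, adjustment reduces the variance by 35% at rho 0.3 and by 5% at rho 0.9. Whether the trial would gain a lot or a little cannot be told from the article, which gives no data on how the changes relate to baseline. The benefit matters most for the Bonferroni-corrected pairwise contrasts: under the assumed d of about 0.84, unadjusted power there is about 79%, and adjustment brings it to between 82% and 94%.

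**What to change.** State the primary analysis as an ANCOVA of the change in MAP on arm with T0 MAP as covariate, and likewise the change in HR with T0 HR. Report adjusted differences between arms with confidence intervals, and Bonferroni-adjusted pairwise contrasts. Fix this model in advance, do not let Shapiro-Wilk choose it, and keep a rank-based analysis as a sensitivity analysis.

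The cost is a change of analysis wording through the route in the Protocol amendments section, before group comparisons are seen. SPSS, the software already named, fits the model. No new data or patients are needed. If an analysis plan that is not shown already specifies this model, the published wording only needs to be aligned with it.

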##### Drop-out criteria

1. Participant’s request to withdraw the study;

2. Occurrence of serious complications or adverse events during the anesthesia;

3. Difficult intubation; and

4. Other reasons that enable the principal researcher to decide to terminate the study.

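### Repeated-measures ANOVA, apparently meant for the secondary T0 to T5 haemodynamic series, uses complete cases only, while the drop-out rules can remove patients for events related to those readings

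*Protocol article*

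**What the plan says.** The Statistical analysis section of the protocol article gives one sentence on continuous outcomes: numerical variables go to one-way ANOVA or "repeated-measures ANOVA or Kruskal-Wallis tests after checking the normal distribution". It ties none of the three tests to a named outcome.

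The Interventions section sets one timed series: SBP, DBP, MAP and HR at baseline (T0), 1 and 3 minutes after induction (T1, T2), at intubation (T3), and 1 and 5 minutes after intubation (T4, T5). The Secondary outcomes section lists these parameters. The primary outcomes, ▴MAP and ▴HR, are each an extreme value compared with baseline, not a profile over time.

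The Drop-out criteria section has four entries. One is "Occurrence of serious complications or adverse events during the anesthesia", another is difficult intubation. The other two are "Participant’s request to withdraw the study" and an open category left to the principal researcher.

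The Sample size section requires 31 patients per group and then says: "Considering an estimated 20% dropout rate, 39 patients in each group will be included in this study". It gives no cause for the 20%.

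**The concern.** Classical repeated-measures ANOVA needs a full set of readings from each patient. A patient whose readings stop at intubation loses T3 to T5 and is then removed from the analysis altogether, so valid T0 to T2 readings are lost too.

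This matters when the reason for stopping is related to what is being measured. Two of the four drop-out criteria are clinical events that can fall inside the measurement window, and in a trial of haemodynamic stability an adverse event is plausibly linked to MAP or HR. If patients with unstable haemodynamics leave more often, those who remain look more stable than the arm really was. If one arm has more such patients, it loses more of them and the difference between arms shrinks. The secondary time profile would then understate the contrast it is meant to show.

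A lesser matter is that the within-patient and group-by-time F tests assume sphericity. That is unlikely for unevenly spaced readings in which neighbours resemble each other more than distant ones.

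**Working it through.** **1. The plan's own figure.** Evaluable number 31 per group and drop-out 20% (Sample size section): 31 / (1 − 0.20) = 38.75, rounded up to 39; 3 × 39 = 117. This reproduces the plan. In reverse, 39 × 0.80 = 31.2, so a complete-case analysis after the full 20% loss still has the required 31. The loss of numbers is covered. What remains is possible bias.

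**2. Can drop-out fall inside the series and relate to it?**
- Serious complication or adverse event during anaesthesia: can fall before T5 and may be haemodynamic. It can also occur after T5, in which case all six readings exist and the patient is not deleted.
- Difficult intubation: falls at about T3. Expected difficult airways are already excluded by the Exclusion criteria.
- Participant's request: cannot be made between loss of consciousness and T5. A withdrawal before induction leaves no T1 or T2 to save.
- Other reasons, at the principal researcher's decision: timing and cause open.

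So a series that stops between T3 and T5 through drop-out would come mainly from the first, second or fourth reason. How many of the 20% are of this kind is not stated.

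**3. How large could the bias be?** The documents give no SD, correlation or effect for the serial readings, so these are assumptions: two arms, SD 12 mmHg, first-order autoregressive correlation 0.7 between successive readings, mean MAP change from T2 onward of −15 and −10 (true difference 5). As an extreme case, the 20% of patients with the lowest T2 value drop out.

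For a normal variable cut off below c, the mean of those kept is μ + σ·φ(a)/(1 − Φ(a)), with a = (c − μ)/σ. The cut-off giving 20% overall is c = −22.8.
- Arm at −15: a = −0.652, drop-out Φ(a) = 26%, upward shift 12 × 0.3226/0.7427 = 5.2.
- Arm at −10: a = −1.068, drop-out 14%, upward shift 12 × 0.2255/0.8573 = 3.2.
- Complete-case difference at T2: 5 − (5.21 − 3.16) = 2.9.
- At T4, two steps later, the shift carries over by 0.7² = 0.49: 5 − 0.49 × 2.06 = 4.0.

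Simulation gives the same values. With means of −18 and −8 (true difference 10), the results are about 6.1 at T2 and 8.1 at T4, with drop-out 31% against 9%.

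A milder version lets drop-out depend on the fall from T0 to T2. The true 5 then becomes about 4.0 at T2 and 4.5 at T4. A likelihood-type estimate using all recorded readings returns about 5.0 at both times.

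If drop-out is unrelated to the readings, the shift is zero. The range is therefore 0 to about 40% shrinkage at T2 and 0 to about 20% at T4. The upper ends attribute all drop-out to haemodynamics.

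**4. Sphericity.** Simulated null trials, 3 × 31 patients, six times, 6,000 runs per setting, nominal 5% group-by-time test:

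| Autoregressive correlation | Uncorrected | Greenhouse-Geisser |
|---|---|---|
| 0.5 | 6.7% | 4.7% |
| 0.7 | 7.6% | 4.8% |
| 0.9 | 10.0% | 5.3% |

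The between-group main effect stays at 4.6% to 5.5% without correction.

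**The case against.** The strongest reply is that nothing in the Statistical analysis section is contradictory, that missing-data handling for a secondary series usually belongs in the analysis plan, and that a mixed model recovers nothing if dropped patients' readings are not kept. The last point stands and shapes the fix. The first two do not settle the matter: the article names a specific method, and needing complete cases is a property of that method, not an omitted detail.

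Some stronger readings are tempting, but the documents do not support them:
- That the plan ties its 20% drop-out to events at intubation. It gives no cause, and only one of the four criteria concerns intubation.
- That about 23 of 117 patients (0.20 × 117 = 23.4) would lose usable readings. Some may leave before induction with nothing to save, and others after T5 with a full series.
- That the group-by-time test will run at 7% to 10%. This assumes an uncorrected F test, which the plan does not state. An epsilon correction is an ordinary part of the method and restores about 5%.
- That treating T0 as one of the time levels is an error. It is a valid analysis; the covariate form is a preference that comes with the better model.
- That the primary result is at risk from this choice. ▴MAP and ▴HR are single values per patient and do not use the serial method.

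The link between the method and the T0 to T5 series is also an inference, though a close one: it is the only serial method named and this is the only series with defined times.

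**Conclusion.** The concern holds in a limited form. By inference, a complete-case method is paired with drop-out rules that can remove patients for reasons related to the readings. The secondary T0 to T5 comparison could therefore be biased toward stability. The size cannot be derived from the documents; under the assumptions above it runs from nothing to roughly 40% shrinkage of an arm difference at T2 and 20% at T4, with the upper ends a deliberate worst case. Power is not the issue, since the inflation to 39 covers the loss. Sphericity is a supporting point only. The change is worth making because complete-case ANOVA requires that missingness not depend on the readings, which is a stronger assumption than the alternative needs, and because it discards valid data.

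**What to change.** State that all readings recorded before a patient drops out are kept and analysed. Replace repeated-measures ANOVA for HR, MAP, SBP and DBP with a linear mixed model for repeated measures: T1 to T5 as outcomes, T0 as covariate, arm, time and arm-by-time as fixed effects, and an unstructured covariance. Report arm differences with 95% confidence intervals at each time. The unstructured covariance also removes the sphericity assumption.

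State that the model assumes data are missing at random given the recorded readings, and report the number and reasons of drop-outs by arm and time so that readers can judge this.

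The cost is a change of analysis wording and slightly more analysis work. SPSS fits the model, and no further patients or measurements are needed.

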### Auditing

In order to review and verify the development of the study throughout the trial period, the research team will hold a weekly meeting and submit a progress report every month.

### Protocol amendments

If necessary, decisions on protocol amendment will be made by the research team and authorized by the ethics committee.

### Dissemination

The database and related materials will be available accessible for the study staff and researchers of the project. Results will be published in open-access peer-reviewed journals within 12 months of completion of the trial.

## Discussion

Patients with cardiac disease often have different degrees of cardiac functional impairment and almost all anesthetic drugs possess capacity to suppress the myocardium and induce vasodilatation, therefore, these patients are prone to developing hypotension during anesthesia induction [17]. Post-induction hypotension is a threatening complication and is associated with increased morbidity and mortality. Considering the importance and impact of hemodynamic changes on complications and outcomes, anesthesiologists should comprehensively consider the effectiveness and safety when selecting anesthetics agents. An ideal induction agent would be one that is easy to administer, has rapid onset and rapid offset, and few adverse effects. However, such an agent does not exist.

Etomidate is a well-known hypnotic agent routinely used for induction of anesthesia [18]. It was previously considered to be superior compared to other anesthetic agents (such as propofol, midazolam, thiopental) for patients with hemodynamic instability owing to its lower inhibition effect on the cardiovascular system [19–21]. However, etomidate may lead to adrenal cortical function inhibition, nausea and vomiting, injection pain, and myoclonic movement, which are some undesirable adverse complications [22, 23]. Therefore, there is a need for anesthetic agents that have a rapid onset of action, short recovery time, and stable cardiovascular profile.

Remimazolam tosilate is an ultra-short-acting GABA-A receptor agonist [24]; a growing number of studies have shown that remimazolam display stable peri-induction hemodynamics, rapid onset, and rapid elimination [25–27], indicating that remimazolam may be a safe agent for patients with unstable pre-operative hemodynamics. A recent study showed that remimazolam was superior to propofol during anesthesia induction in patients undergoing valve replacement surgery [28]. Furthermore, Saito et al. [29] also reported that remimazolam could be used safely in induction and maintenance of anesthesia for cardiac surgery with cardiopulmonary bypass (CPB). Considering the advantages of remimazolam as mentioned above, remimazolam has the potential to be a better choice during induction and maintenance of anesthesia for cardiac surgery. Currently, there are few studies on the effect of remimazolam on hemodynamics during anesthesia induction in cardiac surgery. To the best of our knowledge, this is the first study comparing remimazolam tosilate and etomidate on hemodynamics during anesthesia induction in patients with cardiac disease. Thus, the aim of the study is to compare the effect of remimazolam tosilate and etomidate for anesthesia induction on hemodynamics in patients undergoing valve replacement surgery. This study will provide new clinical practice data for evaluating the effectiveness and disadvantages of remimazolam in the field of cardiac anesthesia.

